#### Statistical analysis

Response and remission rates will be compared using Chi Square tests. Secondary outcomes and cognitive function will be analysed with multiple regression analyses and other suitable statistical methods. ANOVAs and t-test will be made on a LOCF basis. Categorical variables will be analysed using chi square tests. Ordinal variables will be analysed using non-parametric tests in addition to using T tests and ANOVA. Time to remission and/or response will be analysed using survival analysis. The statistical analysis will be done by the scientific research team with assistance from experts in statistics. All patients who receive at least one medication with study medicine or ECT will be included in the analysis of the safety, demographic and baseline characteristic data. An analysis of treatment-emergent adverse events will be performed. All subjects who receive at least one medication with study medicine and provide post - baseline efficacy measurements will be included in efficacy data analyses (intention to treat). We will use last observations carried forward for subjects who leave the study prematurely. Analyses only including patients fulfilling the treatment will also be done. Baseline for all analyses is visit 2 (start of drug or ECT treatment).

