### Description of treatment

#### Method of assigning patients to treatment groups/Randomization

Patients' eligibility will be established before randomization to one of the treatment options. Relevant patients with BD are addressed in order to establish whether they are willing to be screened for the study. The patients must be assigned a patient number and sign the consent form after receiving oral and written information about the study prior to undergoing any study procedures. Patients will be randomized strictly sequentially, as patients are eligible for randomization. If a patient discontinues from the study, the patient number will not be reused, and the patient will not be allowed to re-enter the study.

We perform a stratified randomization separately for each centre using the default random number generator of SPSS 15 with a random seed. The randomization lists are kept concealed from the investigators.

After randomization patients will enter a wash out phase if necessary. The recommended time for patients to be without concomitant medication in contradiction to the study protocol is 5 t 1/2 for patients randomized to ECT and a varying time for patients randomized to treatment as usual.

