### Reporting of adverse events

AEs will be reported starting with the first trial related procedure. They will be reported until intake of the last dose of trial medication or last trial-related procedure. When known, the cause of death of a subject in a clinical trial must be reported as a SAE regardless of whether the event is expected or associated with the study medicines or procedures. All SAE occurring during the clinical trial must be reported to the Clinical Study Team Leader [name] or principal investigator [name] by investigational staff within 24 h. Information regarding SAEs must be reported using the SAE form. The report of a SAE may be made by fax or telephone. A telephone report must be followed by a completed SAE Form.

CATEGORY 1: No change required. This category would be for SAEs which in the estimation of the investigators and the RSA that any relationship to the study intervention is questionable and the chances for harm to the future research subjects is unlikely.

CATEGORY 2: Increased monitoring necessary. This category would be for SAEs in which the RSA Committee would require increased frequency or intensity of monitoring.

CATEGORY 3: Intervention or treatment modifications necessary. This category would be for SAEs that would lead to a recommendation to modify the treatment, for example, lowering the dose of the study drug, or extending the treatment interval.

CATEGORY 4: Temporary or permanent suspension of the study. This category would be for SAEs which are judged to be serious enough that no further subjects should be enrolled or treated until a decision about whether the protocol can continue under some modified circumstances. In order to permanently suspend a protocol, a full review of the events by the RSA Committee and the GCRC Advisory Committee will be undertaken.

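### The safety analysis starts at first treatment although an arm-dependent wash-out follows randomisation, so a randomised patient whose wash-out event prevents treatment is left out of the between-arm comparison

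*Protocol article*

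**What the plan says.** **Order of events.** The section on assigning patients to treatment groups states: "After randomization patients will enter a wash out phase if necessary". It gives the recommended drug-free time as "5 t 1/2 for patients randomized to ECT and a varying time for patients randomized to treatment as usual", and the Wash out Phase section repeats this.

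**Analysis.** Under Statistical analysis the safety set is fixed by exposure: "All patients who receive at least one medication with study medicine or ECT will be included in the analysis of the safety". The next sentence on safety reads: "An analysis of treatment-emergent adverse events will be performed". The same section places baseline for all analyses at visit 2, when drug or ECT treatment begins.

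**Reporting.** The section on reporting of adverse events is wider: "AEs will be reported starting with the first trial related procedure". It adds "All SAE occurring during the clinical trial must be reported", within 24 hours, and "Information regarding SAEs must be reported using the SAE form".

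**Schedule and definitions.** Table 4 marks the SAE form at visits 3 to 8 (weeks 1 to 6), and not at visits 1 or 2. The definition of an adverse event refers to occurrences during treatment with, or administration of, a pharmaceutical product. The section on suicide attempt and suicide covers events connected with use of study medicine.

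**Withdrawal.** The Withdrawal criteria remove a patient whose condition worsens significantly or who meets an exclusion criterion. Table 2 lists high suicidal risk among the exclusion criteria. Every patient who stops early is to have a final evaluation.

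**The concern.** Where a wash-out is needed, it is part of what randomisation assigns: previous medication is withdrawn from severely depressed patients, for a time whose recommended length depends on the arm. A safety set that begins at first treatment is harmless if little can happen between randomisation and that treatment. Here something can happen, and the withdrawal rule makes leaving the set depend on the outcome. A patient who deteriorates or becomes highly suicidal during wash-out is withdrawn, never receives study treatment, and so falls outside the safety analysis because of the event it ought to show.

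Comparing the adverse effects of ECT with those of treatment as usual is a stated aim of the trial. If pre-treatment events differ between arms, a comparison limited to treated patients cannot show it, and the two treated groups are no longer exactly the groups that were randomised.

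**Working it through.** The concern disputes no figure in the plan, so the main check is a comparison of sections.

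1. **Is wash-out after randomisation?** Yes, where one is needed. The order is randomisation, wash-out, visit 2.
2. **Is its length the same in both arms?** Not by rule. ECT has a fixed number of half-lives and treatment as usual a varying time. Neither is given in days, and the text does not say which is longer.
3. **Are wash-out events to be reported?** Yes. Reporting starts at the first trial procedure, which precedes wash-out, and every SAE during the trial goes on the SAE form. That text ties the form to no visit.
4. **Do they enter the safety analysis?** There are two cases.
   - *The patient never starts treatment.* The patient has had neither study drug nor ECT, is outside the safety set, and the event is not compared between arms.
   - *The patient starts later.* The patient is in the set, but an event before first treatment is not treatment-emergent in the usual sense. The article does not define the term, so this second case is an inference.
5. **Do the sections agree on the reporting window?** No. Read literally, Table 4 (SAE form from week 1), the adverse-event definition (during treatment) and the suicide-attempt section (use of study medicine) are all narrower than the reporting rule.

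**Illustration on assumed rates only.** The planned total of 132 reproduces: for a difference of 4, SD 7, two-sided 5% and 90% power, the exact two-sample t-test needs 65.3, so 66, per arm with equal allocation (the ratio is not stated). Assume an on-treatment event risk of 5% in both arms, and that every wash-out event prevents treatment. Let a and b be the assumed wash-out risks under ECT and drug treatment.

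- Patients with events outside the safety set = 66 × (a + b).
- Risk difference in all randomised patients = (a − b) × (1 − 0.05).
- Risk difference in the treated set = 0.05 − 0.05 = 0.

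| a | b | Patients outside the set | Difference, all randomised | Difference, treated set |
|---|---|---|---|---|
| 3% | 0% | 66 × 0.03 = 1.98 | 0.03 × 0.95 = 2.9 points | 0 |
| 5% | 2% | 66 × 0.07 = 4.62 | 0.03 × 0.95 = 2.9 points | 0 |
| 8% | 2% | 66 × 0.10 = 6.60 | 0.06 × 0.95 = 5.7 points | 0 |

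The table shows the mechanism. It does not estimate the gap in this trial: none of these risks comes from the article, and putting the higher risk under ECT is arbitrary.

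**The case against.** The strongest reply is that a treated-patient safety set with a treatment-emergent analysis is normal practice, and that listings of pre-treatment events are often left to an analysis plan or to the full protocol that this article condenses. Much of that is fair, and the set should stay. But the article does not leave the population open. It fixes it, in a design where drug withdrawal of arm-dependent length lies between randomisation and first treatment.

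A second reply is that safeguards already exist. Events are reportable from the first procedure, all overdoses are reported as adverse events, those who stop early have a final evaluation, the depression and mania ratings are taken at visits 1 and 2, and patients already at high suicidal risk are not enrolled. These points stand for recording, and they narrow the scenario. None puts an event in a patient who never starts treatment into the between-arm analysis.

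Three stronger readings are tempting and not supported:

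- A reader might infer from Table 4 that serious events before week 1 go unrecorded. The reporting section says otherwise, and the week-1 form may look back over earlier time. Table 4 shows a conflict to reconcile, not a proven loss of data.
- A reader might work out a share of follow-up that is not covered. That needs wash-out durations the article does not give, it ignores that wash-out happens only if necessary, and the time is covered for reporting.
- A reader might infer that one named arm is favoured. A varying time may be shorter than, equal to or longer than the ECT interval.

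**Conclusion.** The point holds as one about analysis, not about recording. By the stated rule, a randomised patient whose wash-out event prevents treatment is left out of the between-arm safety analysis, and the withdrawal criteria make that exclusion depend on the event itself. Neither size nor direction can be derived from the article, and the gap may be small if few patients need a wash-out. The conclusion rests on reading the safety-set sentence as written. Its extension to wash-out events in patients who do start also rests on the usual meaning of treatment-emergent. No sample-size figure is affected. The change is worth making because it is cheap and uses events the protocol already requires to be reported.

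**What to change.** In Statistical analysis, keep the treated-patient safety analysis and add a sentence such as:

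> Deaths, SAEs and suicide attempts from randomisation to week 6 will be summarised by randomised arm for all randomised patients, including those who never start treatment. Events before first treatment will be shown separately, and wash-out length will be summarised by arm.

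Then reconcile Table 4, the adverse-event definition and the suicide-attempt section with the reporting rule, so that SAE recording plainly covers the time from randomisation to first treatment, including patients seen only at the final evaluation after early discontinuation. Marking the SAE form at visit 2 would not be enough: that visit is the start of treatment, and the patients at issue do not reach it.

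The cost is one extra table and minor wording changes. No dose, wash-out rule or withdrawal rule needs to change for this.

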**Figure 1 F1:**
[figure not shown]
**Flow Chart of Study Design**.

Relevant patients with depression are addressed in order to establish whether they are willing to be screened for the study. The patients must be assigned a patient number and sign the consent form after receiving oral and written information about the study prior to undergoing any study procedures.

Each treatment trial lasts 6 weeks. The medication that would be used if a patient should be randomized to drug treatment will be determined at enrolment, before randomisation. If a patient receives ECT and reaches remission earlier than six weeks, the ECT treatment is terminated and the patient is switched to maintenance therapy. If a patient or the treating clinician decides that the patient could receive better treatment outside of the study, the patient may leave the study at all times, as specified in the informed consent. In case of remission after the six weeks trial the patient continues with maintenance drug treatment at the clinicians decision, guided by relevant algorithm as for example in Goodwin & Jamison 2007 [31]. In case of non- remission the clinician might consider the other treatment condition. This will not be part of the present study.

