Current use of all other psychotropic medication during the study period with the exception of the following: The use of alimemazine (max dose 30 mg daily), chlorpromazine (max dose 25 mg × 2 daily) and chlorprothixene (max dose 20 mg × 2) is allowed. The use of mianserine (max dose 10 mg daily) is allowed. Medication related to the ECT procedure is allowed.
For Medication in control group refer to Medication in control group - Treatment As Usual
Inability to comply with study protocol
Unstable serious medical conditions, including clinically relevant laboratory abnormalities
Conditions that affect neuropsychological assessment such as Parkinson's Disease, Multiple sclerosis, stroke, alcohol and substance abuse or dependence (according to SCID or DSM-IV-TR)
Fertile women without adequate contraception (Adequate contraception includes: abstinence, oral contraceptives, intrauterine devices, barrier method)
Young Mania Rating Scale (YMRS) [43] of 20 or more
Patient at high suicidal risk according to clinicians' judgement

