#### Withdrawal criteria

The patient will be withdrawn from the study if the clinician finds that the patient is in need of, or better served with other treatment, or if Exclusion criteria are met. The patient will also be withdrawn from the study if the clinical condition gets significantly worse according to the clinicians' judgement or if patients withdraw their consent. The date and the reason for discontinuation are noted. All patients prematurely discontinuing the trial must be seen for a final evaluation.

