### Sample size calculation

#### A-priori power calculations

The primary response variable, change in MADRS-score between baseline and endpoint, will be done with the two-sample t-test at the significance level α = 0.05. The least clinical important difference between the treatment group (ECT) and the reference group (drug) to be detected was judged to be 4 in favour of ECT, and a SD = 7 for the change in MADRS is assumed. The possibility of an opposite effect could not be ignored and a two-sided test will be done. Thus the competing hypotheses are:

H0: Mean change in MADRS is the same in both groups vs.

HA: Mean change in MADRS is different in the two groups.

To detect a difference of 4 in mean change in MADRS between the two groups with a power of Π = 0.90 a total of n = 132 patients will have to be included in the analysis. Standard deviations of S= 6-7 are typical for MADRS in studies of patients with BD. The standard deviation for change in score is S√[2(1-R)] where R is the correlation between the two timepoints. Thus, with a correlation of at least 0.5 the standard deviation for the change will be at most S and the power at least 0.90.

Concerning changes in inflammation measures, effects sizes of more than 20-50% are expected, but standard deviations in this population will vary for different cytokines, and a formal power analysis has not been performed.

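### Clinician-judged withdrawal followed by last observation carried forward can bias the primary MADRS contrast in either direction, and MADRS-only definitions let a withdrawn manic patient count as a remitter

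*Protocol article*

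**What the plan says.** All places are in the protocol article.

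- **Primary test.** A-priori power calculations: the comparison of MADRS change "will be done with the two-sample t-test at the significance level α = 0.05". It is two-sided, because "The possibility of an opposite effect could not be ignored and a two-sided test will be done". The difference to detect "was judged to be 4 in favour of ECT".
- **Missing scores.** Statistical analysis: "We will use last observations carried forward for subjects who leave the study prematurely". The same section places t-tests and ANOVAs on this basis. It adds an analysis restricted to patients who complete treatment.
- **Who is withdrawn.** Withdrawal criteria: a patient will be "withdrawn from the study if the clinician finds that the patient is in need of, or better served with other treatment", and likewise on significant worsening in the clinician's judgement or on meeting an exclusion criterion. A final evaluation at exit is required.
- **Relevant exclusion criteria.** Table 2 lists "Young Mania Rating Scale (YMRS) [43] of 20 or more" and "Current use of all other psychotropic medication during the study period with the exception of the following".
- **Masking and candidacy.** The treating psychiatrist knows the allocation (Inclusion, randomization and masking of study groups). An indication for ECT is an inclusion criterion (Table 1), and Methodological weaknesses explains that these patients would probably have had ECT anyway.
- **Early ECT remitters.** Study design, after Figure 1: "If a patient receives ECT and reaches remission earlier than six weeks, the ECT treatment is terminated and the patient is switched to maintenance therapy".
- **Ratings.** MADRS is scheduled weekly to week 6. Table 4 marks audio-taping only at visits 2 and 8.
- **Definitions.** Response is a fall of at least 50% in MADRS. Remission is a MADRS of 12 or less at the end of the trial. Neither has a condition on mania or on completing treatment.

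**The concern.** The grounds for withdrawal are tied to how the patient is doing and are judged by someone who knows the arm. A control patient who is doing poorly has an obvious alternative, ECT, outside the allocated treatment, and patient or clinician may end participation at any time. Exits could therefore differ between arms in number and in timing. When patients are still improving, a carried-forward score understates the change they would have shown at week 6. The arm with more or earlier exits is penalised for leaving rather than for its week-6 result. The primary estimate and its type I error are at stake.

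A second point concerns the rates. A YMRS of 20 or more is an exclusion criterion, and meeting one triggers withdrawal. If that patient's MADRS is 12 or less at exit, nothing in the definitions prevents the carried score from being counted as remission.

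**Working it through.** **1. The plan's own figure.** Inputs from A-priori power calculations: difference 4, SD 7, two-sided α 0.05, power 0.90. Normal approximation: n per arm = 2 × (1.960 + 1.282)² × 7² / 4² = 64.4, so 65. The exact t-test needs 65.3, so 66 per arm and 132 in total. The stated 132 reproduces (power 0.903 at 66 per arm, taking 1:1 allocation, which the article does not state). It leaves no allowance for distortion by early exit.

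**2. Assumptions for the illustration.** The article gives neither dropout rates nor exit times. Assumed: no true difference; both arms improve 12 points linearly over six weeks; exits of 10% in one arm and 20% or 30% in the other. In the simulation, change at week t = (−12 + N(0, 6)) × t/6 + N(0, 3.5). The week-6 SD is √(36 + 12.25) = 6.9, close to the planned 7.

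**3. Exits unrelated to the patient's course.** Spurious difference = (difference in exit proportions) × 12 × (1 − mean exit week / 6).

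| Exit weeks | Shortfall per leaver | 10% vs 20% | 10% vs 30% |
|---|---|---|---|
| 1–3 (mean 2) | 12 × 4/6 = 8 | 0.8 | 1.6 |
| 1–5 (mean 3) | 12 × 3/6 = 6 | 0.6 | 1.2 |
| 3–5 (mean 4) | 12 × 2/6 = 4 | 0.4 | 0.8 |

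With SE = 7 × √(2/66) = 1.22, a shift of 1.6 gives a type I error near 26% by normal approximation and about 24% to 26% by simulation. A shift of 0.8 gives about 10%. Exits over weeks 1–5 give about 8% and 16% to 17%.

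**4. Exits concentrated among poor responders.** The withdrawal rule suggests this pattern. These patients lose less by having their score frozen, and the outcome spread widens. With exits at weeks 1–3, 10% vs 20% gives 0.4 to 0.5 points and type I error at or close to 5%. For 10% vs 30% the figures are about 1.0 to 1.1 points and about 8% to 13%, according to how selection is modelled. Late exits combined with selection give smaller values still.

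**5. Direction.** With 30% exits on ECT and 10% on control, the sign reverses: about 1.5 to 1.6 points against ECT for exits at weeks 1–3 unrelated to course.

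**6. Equal exits.** With both arms linear, 10% vs 10% gives no bias under the null (type I error 0.05). If ECT reaches its full effect by week 3 and control is linear, 20% exits in both arms give 0.2 × C × [(1 − w/6) − (1 − w/3)]. This is 0.33 points for C = 10 and w = 1, and 1.5 points for C = 15 and w = 3, in favour of ECT. C is the week-6 change and w the exit week.

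**7. When a true effect exists.** Take true changes of 16 and 12 points and 20% exits in each arm at weeks 1–3. The expected difference is 4 × (1 − 0.2 × 4/6) = 3.47. Carrying forward also widens the SDs, to about 7.8 and 7.2 in simulation. SE = √[(7.8² + 7.2²)/66] = 1.31, and power is about 0.74 rather than 0.90.

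**8. Remission.** Each withdrawn manic patient counted as a remitter adds 1/66 = 1.5 percentage points to that arm's rate.

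**The case against.** Several points on the other side stand.

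- **The bias need not favour ECT.** A reader might infer that it must, because control patients have a reason to leave. The documents give no exit rates or times, and the withdrawal grounds apply to both arms. Excess control exit is plausible but not established.
- **The largest figures are not typical.** They need a 20-point gap in exits, early exit, and leavers who resemble those who stay. If poor responders leave, type I error is far lower.
- **Early ECT remitters are not shown to be carried forward.** It is tempting to combine the switch to maintenance medication with the exclusion of other psychotropics and the withdrawal rule, and to conclude that these patients leave and any relapse goes unseen. The article ends their ECT but does not say they leave the study; it treats leaving separately, and it schedules weekly MADRS to week 6 without exception. What remains is a gap in wording between those sections.
- **The mania problem is not mainly a product of carrying forward.** The MADRS-only definitions would classify such a patient the same way on an observed score. Mania is also captured by weekly YMRS and CGI-BP, by the new-episode definition and by adverse events. The explicit link to carrying forward names t-tests and ANOVAs; its use for the rates rests on the general sentence.

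The other safeguards help less. The final evaluation updates the score only to the exit date. The completers-only analysis selects on the same exits. Time-to-event analyses are secondary. A fuller protocol might provide for ratings after exit, but the article fixes the carry-forward rule for everyone who leaves early.

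**Conclusion.** The point holds as a defect in the primary analysis rule. Outcome-related withdrawal under unmasked judgement, followed by carrying the last score to week 6, can bias the contrast whenever exit rates, exit times or speed of response differ between arms. Under the assumptions shown (10% vs 20–30% exits, 12 points of linear improvement, no true difference), the spurious difference is about 0.4 to 1.6 points, or 10% to 40% of the 4-point target. It favours the arm with fewer exits when both arms improve at the same pace. Type I error ranges from nominal to about 24%. Equal random exits of 20% at weeks 1–3 would cut a true 4 to about 3.5 and power to about 0.74. These are illustrations, not predictions.

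The classification of a withdrawn manic patient as a remitter is a separate, smaller weakness in secondary outcomes, worth 1.5 percentage points per case. The documents do not support saying that the bias necessarily favours ECT, or that the scores of early ECT remitters are carried forward.

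**What to change.** 1. **Primary analysis.** Use a mixed model for repeated measures on the weekly MADRS, or multiple imputation from those scores, and keep carrying forward as a sensitivity analysis only. Both methods assume that exit is explained by the recorded data, so sensitivity analyses for departures from that are still needed. Since only visits 2 and 8 are marked as taped, state which ratings enter at the intermediate visits.
2. **Follow-up.** Separate stopping allocated treatment from leaving the study. Continue the scheduled ratings to week 6, taped at week 6, for everyone who has not withdrawn consent.
3. **Estimand.** State how scores after a switch to the other treatment are used. If all observed scores count, control patients who receive ECT dilute the contrast; if not, say how those scores are replaced.
4. **Rates.** In the analysis, count withdrawal for mania or for worsening as non-response and non-remission.
5. **Consistency.** Reconcile Study design and Maintenance-treatment after ECT-course with Table 2 and Withdrawal criteria, so that it is clear that ECT patients moved to maintenance medication before week 6 remain in the study and are rated at week 6. No change to clinical management is proposed.

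The cost is amendment and analysis-plan wording, some visits by patients off allocated treatment within the existing schedule, and the possible dilution noted in item 3. The change to follow-up must be made while patients can still be rated, because a week-6 score that was never taken cannot be recovered.

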### Inclusion, randomization and masking of study groups

All patients suffering from a major depressive episode admitted to one of the nine study centres are evaluated for inclusion. During the screening the local participating psychiatrist will determine whether the patient fulfils the inclusion criteria and none of the exclusion criteria. Patients will be randomly assigned to the two groups. The randomization is stratified separately in each study centre. The patient and treating psychiatrist are unmasked about treatment modality. The assessments of depressive symptoms before and after ECT will be audio-taped. The audio-tapes will be co-rated by trained study personnel who are not involved in the treatment of the study patients. The analyses will be preformed on audio taped scores. There might be some patients who do not accept audio taping, in these cases investigator-rating will be used. Neuropsychological assessment is performed by trained test assistants who are blinded about treatment modality.

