## Assessments

An overview of variables is shown in table 4.

**Table 4 T4:** Variable overview

	Study visit	1	2	3	4	5	6	7	8	9	10	Comment
	Week	-5t_1/2_	0	1	2	3	4	5	6	26	**30-52 **^1)^	^1) ^in euthymic phase
	Test											
	Informed consent	X										
Diagnostic interview	SCID or MINI plus	X										
	Inclusion/exclusion criteria	X										
NORBRAIN Entry Questionnaire NEQ	Socio demography Medical history etc	X										
	PANSS	X										
	GAF	X							X	X	X	
	Clinical examination	X										
	Current and concomitant medication	X	X	X	X	X	X	X	X	X	X	
Health related Quality of Life	SF 36	X							X	X	X	
Efficacy	MADRS	X	X^2)^	X	X	X	X	X	X^2)^	X	X	^2) ^audio taped
	IDS	X	X^2)^	X	X	X	X	X	X^2)^	X	X	^2) ^audio taped
	CGI-BP	X	X	X	X	X	X	X	X	X	X	
	PGI-I			X	X	X	X	X	X	X	X	
	YMRS	X	X	X	X	X	X	X	X	X	X	
	MSIF	X								X	X	
Relapse	Interview									X	X	
Overall cognitive function	MMS ^3)^		X	X	X	X	X	X	X			^3) ^in ECT-group only
Neuropsychological assessment		X							X	X	X	
	EMQ	X							X	X	X	
Adverse events	Interview UKU		X^4)^			X			X			^4) ^previous med.
	SAE-form			X	X	X	X	X	X			
Lab	Cytokines	X							X	X	X	
	Cortisol ^5)^								X			^5) ^morning cortisol in blood
	Other, incl cortisol^6)^	X										^6) ^as specified in Blood samples
	ECG ^7)^	X										^7) ^if indicated
	EEG	X										
	MRI caput	X										
Substance abuse	Urin	X										
Pregnancy	Urin ^8)^	X										^8) ^fertile woman
Compliance	Interview			X	X	X	X	X	X	X	X	
Compliance	Blood sample					X						
Temperament	TEMPS-A									X		
Migrene	Interview	X								X		

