### Methodological weaknesses

The use and policy regarding ECT differs between countries and hospitals. Thus there are no published guidelines defining objective clinical criteria for indications of treatment with ECT in bipolar depressions. In the present protocol "indication for ECT" is one of the inclusion criteria. This means that treatment with ECT would have been probable according to hospital practice regardless of the present study.

The assessments are performed by specially trained research staff which is not blinded for grouping of the patients. Most of the patients are acutely admitted to psychiatric acute wards due to the extensive symptom pressure.

The multicentre site design has potential problems regarding assessments and inter-rater reliability. However, multicentre design is a necessity in order to include sufficient number of patients in a reasonable time span. All raters and participants in the study have taken part in mutual training-sessions in the different assessments and rating scales. All participants have taken part in interrater-scorings. The scorings for the different study centres and the different participants are satisfactory.

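### Baseline for all analyses is fixed at visit 2, after randomisation and any arm-dependent washout, and six outcome measures have no visit 2 value

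*Protocol article*

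**What the plan says.** The Statistical analysis section sets one baseline for everything: "Baseline for all analyses is visit 2 (start of drug or ECT treatment". The primary response variable is the change in total MADRS from baseline to endpoint, compared by a two-sided two-sample t-test. Response is a halving of baseline MADRS. Remission is an absolute score of 12 or less and does not use baseline.

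On the order of events, the section on assigning patients to treatment groups has eligibility settled before randomisation, and then: "After randomization patients will enter a wash out phase if necessary". It gives the recommended drug-free time as "5 t 1/2 for patients randomized to ECT and a varying time for patients randomized to treatment as usual"; the Wash out Phase section repeats this.

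On masking: "The patient and treating psychiatrist are unmasked about treatment modality". Methodological weaknesses adds: "The assessments are performed by specially trained research staff which is not blinded for grouping of the patients". Against that, MADRS and IDS are audio-taped at visits 2 and 8, and "The audio-tapes will be co-rated by trained study personnel who are not involved in the treatment of the study patients". The taped scores are the ones analysed. The investigator's rating is used when a patient refuses taping.

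Table 4 marks MADRS, IDS, CGI-BP and YMRS at both visit 1 and visit 2. GAF, SF-36, MSIF, the neuropsychological assessment, EMQ and cytokines are marked at visit 1 and not at visit 2.

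**The concern.** A baseline is useful in a randomised comparison because allocation cannot have influenced it. A visit 2 value lacks that property. Between randomisation and visit 2 the patient learns the arm and may stop medication for a time that depends on the arm. Either can move MADRS. If the arms have moved apart by visit 2, subtracting visit 2 builds that difference into the estimated treatment effect. It also moves the response threshold, by half a point for each point of visit 2 MADRS.

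The second problem is one of execution. The functioning, quality-of-life, cognitive and inflammation aims rest on measures for which the stated baseline is never collected. The section on initial subject characteristics lists GAF and SF-36 among the baseline assessments, which contradicts a visit 2 baseline for every analysis.

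**Working it through.** **1. Position of visit 2.** Table 4 places the inclusion and exclusion check, with MADRS, at visit 1. Randomisation follows eligibility, washout follows randomisation, and visit 2 is the start of treatment. Visit 1 is therefore the pre-randomisation assessment. Table 4 does not show the randomisation point, so this order is read from the text.

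**2. The plan's own sample size.** Inputs from the A-priori power calculations: difference 4, SD of change 7, two-sided α 0.05, power 0.90, total 132. The allocation ratio is not stated; 1:1 is assumed.
- Normal approximation: n per arm = 2 × (1.960 + 1.282)² × (7/4)² = 64.4, so 65 per arm and 130 in total.
- Exact t-test: 65.3, so 66 per arm and 132 in total. The stated figure is reproduced; power at 66 per arm is 0.903.

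**3. How a shift at visit 2 enters.** Write the contrast as

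(week 6 difference between arms) − (visit 2 difference between arms).

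If events after randomisation create a visit 2 difference b, the contrast departs from the effect counted from randomisation by exactly b.

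**4. Size, for an assumed b.** SE = 7 × √(2/66) = 1.2185. The rejection probability comes from the noncentral t distribution with 130 degrees of freedom and noncentrality b/SE. The last column takes a true difference of 4 with the shift working against it, so an apparent difference of 4 − b.

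| Assumed b (MADRS points) | b/SE | Two-sided type I error | Power if b opposes a true 4 |
|---|---|---|---|
| 0 | 0 | 0.050 | 0.903 |
| 0.5 | 0.41 | 0.069 | 0.814 |
| 1 | 0.82 | 0.129 | 0.686 |
| 1.5 | 1.23 | 0.231 | 0.531 |
| 2 | 1.64 | 0.371 | 0.371 |

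One point is 1/4 = 25% of the target difference. No value of b can be taken from the article.

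**5. Coverage of the rule.** The secondary list names seven scales. IDS, CGI-BP and YMRS have a visit 2 value. GAF, SF-36 and MSIF do not. PGI-I starts at visit 3, but it rates change and needs no baseline of its own. So 3 of the 6 scales that need a baseline lack the stated one. Outside that list, the neuropsychological battery, EMQ and cytokines also lack it, which makes six measures in all.

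**The case against.** The best defence is that visit 2 isolates the treatment phase. If a washout shift persisted to week 6, change from visit 2 would remove it and change from visit 1 would carry it. The sentence defining baseline, with its reference to the start of treatment, suggests that this was the intention. That is a legitimate question, but its answer conditions on a measurement taken after randomisation, so it is better placed as a sensitivity analysis.

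The mitigation is also real. Washout applies only where necessary, so any mean shift from it is diluted by patients who have none. Co-rating from tape by staff outside the treatment team limits rater expectation at visit 2. It does not affect true symptom change or what the patient reports after learning the arm, and the article does not call the tape raters blinded.

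Three stronger readings are tempting and not supported:
- A reader might infer that most secondary measures lack a visit 2 value. Among the listed scales that need a baseline it is exactly half. Of all 12 listed secondary items, 7 rest on a scale measured at visit 2 (IDS, CGI-BP, YMRS and the four MADRS-derived response and remission items).
- A reader might infer that the cognitive and quality-of-life aims have no baseline data. They have visit 1 values; only the wording of the rule excludes them. Those values also precede randomisation, so the bias described for MADRS does not arise there.
- A reader might take 13% or 37% as the trial's type I error. These follow from chosen shifts of 1 and 2 points, not from anything in the article.

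Finally, visit 1 MADRS has weaknesses of its own, taken up with the fix.

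**Conclusion.** The point holds in two parts. First, for MADRS the stated baseline is a post-randomisation value, taken with allocation known and after any washout whose recommended length differs by arm. The primary change score and the response rule are therefore exposed to arm differences that arise before treatment starts. Neither the size nor the direction of such differences can be derived from the article. Under the plan's SD of 7, 66 per arm and an assumed 1:1 ratio, 0.5 to 2 points corresponds to a type I error of about 7% to 37% for the effect counted from randomisation. Remission at endpoint is not affected. Second, the rule cannot be carried out for GAF, SF-36, MSIF, the neuropsychological battery, EMQ and cytokines. This is an internal contradiction in the text, easily repaired, and not a gap in data collection.

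**What to change.** Replace the single baseline sentence with a definition by measure:
- GAF, SF-36, MSIF, neuropsychological battery, EMQ and cytokines: baseline is visit 1, the pre-randomisation assessment.
- MADRS: visit 1 is the baseline in the primary comparison, preferably as a covariate for week 6 MADRS, and the reference for the 50% response rule.
- Report visit 2 MADRS by arm, and keep change from visit 2 as a sensitivity analysis.

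The cost is a few lines of text, since visit 1 values are already scheduled. Under the stated inputs N = 132 does not change. There are two downsides. Visit 1 MADRS is rated live rather than from tape and decides the eligibility cut-off of 25, so the mix of rating methods and regression to the mean may alter absolute change and response rates. Both act before allocation and should affect the arms alike. Its correlation R with week 6 may also be somewhat lower than that of visit 2, and the plan's power statement needs R of at least 0.5 because the SD of change is S√[2(1 − R)]. The covariate form eases this: with equal SDs at both visits, as the plan's formula assumes, the residual SD is S√(1 − R²), which never exceeds S. For S = 7 and an illustrative R = 0.4, the SD of change is 7 × √1.2 = 7.67 and the residual SD is 7 × √0.84 = 6.42.

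Separately, the statements on washout length in the exclusion criteria, the randomisation and Wash out Phase sections and the visit 1 column of Table 4 differ on whether five half-lives applies to both arms, and must be reconciled.
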